### 13.5 Protocol Violations

Protocol violations are major deviations from the procedures outlined in this document, and may include

**Confidential**

- the intake of concomitant medications not permitted during the trial
- missed evaluations
- non-compliance with the IMP (e.g. intake of trial drug < 1.5 g daily during treatment period (week 3-6), depending on the duration of intake per treatment period and drug counting)
- any non-adherence to the protocol that would have an impact to the subject's rights, safety or welfare.

Minor protocol deviations may include, but are not limited to, e.g.:

- intake of trial drug < 5 g daily and > 1.5 g daily during the treatment period (week 3-6), depending on the duration of intake per treatment period
- unscheduled visits

After a subject has been enrolled, it is the investigator's responsibility to make a reasonable effort to correct any protocol violations and to continue the subject's participation in the trial. Protocol violations do not justify withdrawal of a subject from the trial.

Protocol violations will be reported to the sponsor/sponsor delegated person during the course of the trial in the monitoring reports.

Protocol violations will be listed and the impact on the evaluation of the subjects concerned will be discussed and evaluated at regular time intervals (depending on the amount of protocol violations), and prior to unblinding for a statistical analysis. Handling of major deviations in statistical analyses will be fixed during a blinded data review before unblinding.

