### 16.2 Termination of the Trial for Individual Subjects

If the clinical trial is prematurely terminated or suspended for any reason, the investigator should promptly inform the subjects and ensure appropriate therapy and follow-up.

Where required by the applicable regulatory requirements, the competent authority(ies) and the ethics committee(s) will also be informed.

There are different grades of deviations from the study flow ranging from minor, major protocol violations, (such as delayed or unscheduled study visits, discontinuation of taking the study drug, taking medication listed under prohibited therapy / concomitant medication (see protocol violations section 13.5) to complete withdrawal. Complete withdrawal should be a rare exception.

Whenever a subject is withdrawn totally from the trial, a complete final examination as scheduled for the premature termination/dropout visit should be conducted, and the circumstances of the withdrawal or discontinuation have to be recorded in detail in the medical file and the CRF.

If a subject does not return for a scheduled visit, every effort should be made to contact the subject (e.g. by *telephone visit* to assess and document treatment compliance, safety, or concomitant medication/ therapy) in order to avoid loss-to follow-up or dropout. These efforts have to be documented in the medical file.

Regardless of any decision to modify or discontinue their assigned intervention, study participants should be retained in the trial whenever possible to enable follow-up data collection and prevent missing data. In any circumstance, every effort should be made to document (key) subject outcomes, if possible. The subject has to be requested to return all unused investigational product(s), if applicable, and followed-up regarding any unresolved adverse events.

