### 16.2.2 Termination by the Investigator

Subjects may also be withdrawn at any time at the discretion of the investigator for safety, behavioral, or administrative reasons, e.g.

- Occurrence of intolerable adverse events and which would constitute an unacceptable high risk for the subject
- Medically indicated e.g. because it is found that inclusion/ exclusion criteria were violated
- Continuation is unacceptable because risks outweigh the benefits
- Pregnancy
- Lack of compliance of the subject (e.g. taking prohibited medication)
- Significant protocol violations
- Logistical reasons (e.g. subject changes his/her doctor or hospital or moves to another location)

Whenever a subject is withdrawn from the trial, the reasons of the withdrawal or treatment discontinuation together with the date of last intake have to be recorded in detail in the patient's medical records and the CRF. If a patient drops out totally from the study and no data will be collected after withdrawal, a complete final examination (dropout visit, see 10.2.6) should be conducted. In particular, every effort should be taken to assess the primary outcome. The subject has to be requested to return all unused investigational product(s), if applicable, and followed-up regarding any unresolved adverse events.

If a subject does not return for a scheduled visit, every effort should be made to contact the patient in order to regain him for further visits according to the protocol.

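### Section 13.5 rules out withdrawal for protocol violations, but two grounds in section 16.2.2 allow it, so later SARA values, mainly period 2, can be lost avoidably (minor)

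*Protocol*

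**What the plan says.** Protocol section 13.5 defines protocol violations as major deviations. Its examples include taking concomitant medication that is not permitted and non-compliance with study drug. It asks the investigator to try to correct violations and keep the subject in the trial, and ends: "Protocol violations do not justify withdrawal of a subject from the trial".

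Section 16.2.2 opens with "Subjects may also be withdrawn at any time at the discretion of the investigator" and gives example reasons. Two of them are "Lack of compliance of the subject (e.g. taking prohibited medication") and "Significant protocol violations". A third is "Medically indicated e.g. because it is found that inclusion/ exclusion criteria were violated". The section foresees that a patient may drop out totally with no later data. For that case it asks for a drop-out visit and says that "every effort should be taken to assess the primary outcome".

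Other sections bear on which rule applies:

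- Section 16.2, the parent of 16.2.2, grades deviations from minor and major violations up to complete withdrawal. It refers prohibited medication to 13.5 and says "Complete withdrawal should be a rare exception". Whatever is decided about the intervention, "study participants should be retained in the trial whenever possible to enable follow-up data collection and prevent missing data".
- Section 9.11.3 also refers regular intake of prohibited drugs to 13.5.
- Sections 10.2.6 and 16.2.1 let a patient who stops treatment in period 1 enter period 2 after the wash-out.
- Section 10.2.6 puts the drop-out visit 4 weeks after the last dose.
- Section 13.4 analyses by randomised sequence regardless of violations, and section 13.6 uses all observed data without imputation for the primary analysis.

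**The concern.** The same events are excluded as reasons for withdrawal in one section and offered as reasons in another. A site that follows 16.2.2 can stop the SARA visits of a patient whom 13.5 would keep. That removes data which the intention-to-treat analysis is meant to include.

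In a crossover the cost per patient is high: withdrawal before visit 5 removes the whole second period and with it the within-patient comparison. The planned sensitivity analyses for missing data can probe such gaps but cannot fill them. This is a rule of conduct, so an analysis plan cannot repair it later.

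**Working it through.** **1. The two rules side by side**

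| Event | Section 13.5 | Section 16.2.2 |
|---|---|---|
| Prohibited medication | violation; no ground for withdrawal | named as an example of lack of compliance; ground for withdrawal |
| Non-compliance with study drug | violation; no ground for withdrawal | lack of compliance; ground for withdrawal |
| Major deviation in general | violation; no ground for withdrawal | significant violation; ground for withdrawal |

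**2. The protocol's sample size (section 13.3)**

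Inputs: difference 1.5, SD of the paired difference 4.2, two-sided 0.05, 90% power. The exact noncentral-t calculation gives n = 85. At n = 86 the noncentrality is 1.5/4.2 × √86 = 3.31 and power is 90.6%. Dropout: 86/0.80 = 107.5, so 108. The plan's figures reproduce. The budgeted loss is 108 − 86 = 22 patients, or 22/108 = 20.4%.

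The protocol gives no rate of withdrawal for violations. If withdrawals came on top of the 20% (assumed rates, withdrawn patients counted as contributing nothing):

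| Extra loss | Completers | Power |
|---|---|---|
| 2 points | 84 | 89.9% |
| 5 points | 81 | 88.8% |
| 10 points | 75 | 86.3% |

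**3. What one withdrawn patient loses**

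The primary model (section 13.1) uses 2 visits × 2 periods = 4 change scores. If SARA is taken at the visit where withdrawal occurs, 1 of 4 remains after visit 3, 2 of 4 after visit 4, 3 of 4 after visit 6 and 4 of 4 after visit 7.

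Under-dosing in weeks 3-6 would normally show in the tablet count at visit 4 or 7 (section 9.7), where SARA is taken anyway. On that ground, period 2 is lost after visit 4 and nothing for the primary analysis is lost after visit 7. Prohibited medication noticed mid-period can also cost the week-6 value.

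**4. Information on the week-6 contrast, for scale**

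Assumptions: each change score has variance s²; all scores within a patient share correlation r (random intercept); visit means week 2 versus week 6; there is a treatment-by-visit interaction; one-period patients are balanced over treatments and most patients are complete.

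- Complete patient: the treatment differences at weeks 2 and 6 are uncorrelated, each with variance 2s²(1−r). Information is 1/[2s²(1−r)].
- Period-1-only patient: the diagonal term of the added information matrix is 1/[4s²(1−r²)].
- Ratio: 2(1−r)/[4(1−r)(1+r)] = 1/[2(1+r)].

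At the stated r = 0.6 this is 1/3.2 = 31%. The stated SDs of 3.0 and 4.2 imply r = 1 − 4.2²/(2 × 3.0²) = 1 − 17.64/18 = 0.02, which gives 1/2.04 = 49%. Both values are shown because section 13.3 does not fix one.

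The model's covariate averages the two period baselines. A patient withdrawn before visit 5 has no second baseline. Unless that is handled otherwise, the covariate cannot be formed and the contribution may be zero.

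**5. The drop-out visit as a substitute**

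It falls at last dose + 28 days. A last dose at visit 3 (day 14 ± 5, so days 9-19) puts it on days 37-47. That coincides with the visit 4 window (42 ± 5), but the patient is 28 days off drug. A last dose on days 20-42 puts it on days 48-70, outside that window. Neither is an end-of-treatment value, and neither supplies period 2.

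**The case against.** The strongest reply is that the protocol does show which rule it means. Sections 9.11.3 and 16.2 both send prohibited medication to 13.5. Section 16.2 places violations below complete withdrawal and asks for retention. The reasons in 16.2.2 are permissive examples under that parent text. Section 16.2.2 also mentions treatment discontinuation alongside withdrawal and treats total dropout as a separate, conditional case, so a site could read the two grounds as stopping drug only. All of this stands, and it lowers the risk. It does not remove the conflict: 16.2.2 comes under termination of the trial for individual subjects, speaks of subjects being withdrawn, and keeps both grounds on its list.

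The reply is also right that the consequence is limited. A reader might infer that the primary result will be biased or the trial underpowered. The protocol does not support that: it gives no violation rate, plans sensitivity analyses for informative missingness, and budgets for 20% loss. A reader might also put a one-period patient at (1−r)/2 = 20% of a complete patient's information. That treats each period as a single value and does not fit the stated model with two visits per period.

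Finally, a fix that capped the two grounds without a safety exception would create a new mismatch, because violations under 13.5 include those affecting a subject's safety or welfare. The exception therefore has to stand in both sections.

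**Conclusion.** The inconsistency is real, and its weight is minor. The protocol's intent leans towards 13.5, but two grounds in 16.2.2 authorise what 13.5 excludes, and a site using them can lose SARA values avoidably, mainly those of period 2.

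No size or direction of bias follows from the document. Power stays at the planned level while total losses remain within 22 of 108. The 31% to 49% per patient is an indication of scale only. It rests on a common within-patient correlation, balance over treatments, and the patient entering the model despite the missing second baseline.

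**What to change.** In section 16.2.2, state that lack of compliance and significant protocol violations justify at most stopping study drug. All scheduled SARA visits and entry into period 2 continue unless withdrawal is needed on safety or medical grounds. Leave the other reasons in that list as they are.

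In section 13.5, add the same safety and medical exception to the sentence on withdrawal, including eligibility violations found later, so that both sections give one rule.

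The cost is the rewording of two list items and one added clause. The visits are already scheduled and sections 10.2.6 and 16.2.1 already allow entry into period 2 after treatment is stopped in period 1, so no procedure is added.

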### 13.6 Handling of Dropouts, Withdrawal, and Missing Data

Subjects dropping out of the trial prior to randomization will be listed including the reason for dropout.

Subjects dropping out totally from the study or merely from the study assigned treatments after randomization will be analysed using all available data. No multiple imputation techniques will be performed for the primary efficacy analysis which is based on an "all observed data approach".

For secondary analyses, dropouts will be included, following ITT principles, by modern imputation techniques for missing data assuming ignorable missingness (e.g. by using the multiple imputations by chained equations (MICE)-approach). For per-protocol analyses, missings will not be imputed.

Sensitivity analyses will be performed to explore several testable and untestable assumptions including various scenarios of informative missingness, in order to assess the robustness of the overall trial result. A detailed description of the applied methods to investigate assumptions concerning missingness will be provided in the *statistical analysis plan*.

**Confidential**

## 14 Data Collection, Handling and Record Keeping

Data management shall be performed by the Institute for Medical Informatics, Biometry and Epidemiology; LMU (IBE). All procedures have to follow Good Clinical Practice (GCP), existing standard operating procedures (SOP) and local laws and regulations as applicable.

### 14.1 Data Management

Details concerning data management procedures and query management will be described in a *data management* and *data validation plan*.

For the transfer of paper-based study data to the study database (eCRF if applicable) double data entry will be performed by two different persons. The two data entries will then be compared for data verification. An audit trail will be created to provide an electronic record of which data were entered or subsequently changed, by whom and when.

SAS software will be used to set up the trial (master and derived) database, and to review the data for completeness, consistency and plausibility. The checks to be programmed will be specified in the *data validation plan*. After running the check programs, the resulting queries will be sent to the investigator for clarification. All programs which can be used to influence the data or the data quality will be validated (e.g. check programs, programs used to import external data, etc.).

### 14.2 Data Coding

Coding of adverse events, medical history and concomitant diseases will be done according to the following coding systems:

- MedDRA

### 14.3 Documentation of Trial Data

#### 14.3.1 Documentation of Trial Data in the Medical Record

The investigator will record the participation in the trial, the frequency of the trial visits, the relevant medical data, the concomitant treatment and the occurrence of adverse events in the medical record of each subject. The SARA and SCAFI scores will be documented by the investigator on source data worksheets that will be provided by the sponsor delegated person. The worksheets should be filed as source documents in the medical records of the respective subject.

The self-administered QoL questionnaires, BDI-II and FSS filled in by the patient will be filed as source data in the respective patient's records. The original file will be provided to the data management for database entry.

Data collected on the CRFs must match the source data. These may include but are not limited to the hospitals' or the physician's medical files, laboratory and pharmacy records, diaries etc.

### **14.3.2 Case Report Form (CRF)**

CRFs provided by the sponsor will be used to document the subject's data during the course of the trial. The data will be pseudonymized, processed and stored according to local law. This also allows preservation for future use.

The investigator has ultimate responsibility for the accuracy, authenticity, timely collection and reporting of all clinical, safety, laboratory data entered on the CRFs. All these data may only be entered and updated in the CRFs by authorized trial personnel.

In case of paper CRFs the completed pages will be sent to the data management for data entry and will be transferred to the sponsor delegated person at the end of the trial. A copy of each CRF page is archived at the investigator's site. The CRFs must be signed by the investigator or by an authorized staff member (physician) to confirm the correctness of the data documented on the CRF. Any corrections to entries made in the CRFs, source documents must be dated, signed and explained (if necessary) and should not obscure the original entry.

Changes are recorded (audit trail) and have to be annotated, once the respective CRF has been marked as completed.

After data cleaning (see section 14.1) and blinded data review, the data base will be locked and be used for unblinded statistical analysis.

Copies of the completed query forms will be stored per subject together with the CRF at the trial site.

### **14.4 Trial site File**

The Trial site will be provided with a trial site file (ISF) containing all sponsor-specific essential and trial specific documents. The monitor will regularly check the trial site file for accuracy and completeness. The trial site file has to be stored locked and sure.

The ISF includes the subject identification list, where the investigator has to record the trial participation of each subject. This list allows identification of each subject and contains the subject number, the name, birth date and the date of inclusion (date of informed consent) of the subject into the trial, and will be reviewed by the monitor for completeness. After end of the trial the subject identification list remains with the study site (this information is not transferred to the sponsor). In addition, trial participation of the subject should be recorded in the Subject Screening and Randomization Log (where patients are pseudonymized, this can be transferred to the sponsor).

The investigator should maintain a list of appropriately qualified persons to whom he/she has delegated trial duties. This list (Team Delegation Log) will be provided with the ISF, too.

**Confidential**

Furthermore, trial personnel responsible for documentation in the CRFs should be identifiable. Therefore a signature list with the name, signature, initials/abbreviation and trial responsibilities of all persons who are allowed to make entries into the CRF will be filed in the investigator's site file.

The trial documents provided by the sponsor are confidential and may not be made accessible to third parties not involved in the trial by the investigator or other staff members. All trial data are collected with subjects pseudonymized.

## **14.5 Archiving**

In case of studies with marketed IMPs consider the requirements described below.

### **14.5.1 Sponsor**

The sponsor must retain all essential documents inclusively the case report forms for the duration of at least 10 years after end or stop of trial. The sponsor must archive all trial related documents according to regulatory requirements.

### **14.5.2 Investigator**

The investigator should maintain all subject documents as specified in Essential Documents for conduct of a clinical trial (see ICH-GCP, section 8) and as required by the applicable regulatory requirement(s) after completion of the clinical trial so that they will be available for audits and inspections by the authorities. The investigator will be responsible for the storage.

The following retention periods will apply after completion or stop of the clinical trial:

- all essential documents and trial related data must be retained securely for at least 10 years (GCP-V § 13 (10),
- the subject identification list for at least 15 years,
- medical records and other source documents for the longest possible period allowed by the hospital, the institution or the private practice.

The investigator/institution should take arrangements to prevent accidental or premature destruction and illegitimate access to these documents.

To enable evaluations and/or audits from regulatory authorities or the sponsor, the investigator agrees to keep records, including the identity of all participating subjects (sufficient information to link records, e. g. CRFs and hospital records), all original signed informed consent forms, copies of all CRFs, serious adverse event forms, source documents, and detailed records of treatment disposition, drug accountability and adequate documentation of relevant correspondence (e. g. letters, meeting minutes, telephone calls reports).

## 15 Reporting

### 15.1 Statistical Report

The statistical analyses and the statistical report are performed, evaluated and approved by [name]. [name], Institute for Medical Informatics, Biometry and Epidemiology. All data in this report are strictly confidential.

## 16 Definition of End of Trial

### 16.1 Regular End of the Trial

The regular end of the trial is defined as "Last Patient Last Visit".

### 16.2 Termination of the Trial for Individual Subjects

If the clinical trial is prematurely terminated or suspended for any reason, the investigator should promptly inform the subjects and ensure appropriate therapy and follow-up.

Where required by the applicable regulatory requirements, the competent authority(ies) and the ethics committee(s) will also be informed.

There are different grades of deviations from the study flow ranging from minor, major protocol violations, (such as delayed or unscheduled study visits, discontinuation of taking the study drug, taking medication listed under prohibited therapy / concomitant medication (see protocol violations section 13.5) to complete withdrawal. Complete withdrawal should be a rare exception.

Whenever a subject is withdrawn totally from the trial, a complete final examination as scheduled for the premature termination/dropout visit should be conducted, and the circumstances of the withdrawal or discontinuation have to be recorded in detail in the medical file and the CRF.

If a subject does not return for a scheduled visit, every effort should be made to contact the subject (e.g. by *telephone visit* to assess and document treatment compliance, safety, or concomitant medication/ therapy) in order to avoid loss-to follow-up or dropout. These efforts have to be documented in the medical file.

Regardless of any decision to modify or discontinue their assigned intervention, study participants should be retained in the trial whenever possible to enable follow-up data collection and prevent missing data. In any circumstance, every effort should be made to document (key) subject outcomes, if possible. The subject has to be requested to return all unused investigational product(s), if applicable, and followed-up regarding any unresolved adverse events.

